### Data monitoring and study safety

A Data Monitoring and Safety Committee (DMC) will be established before the study begins. The committee will periodically review safety data and make recommendations on whether to continue, modify, or stop the study based on the observed results. The DMC will be independent from the study sponsor and competing interests to ensure unbiased evaluation.

A trial monitoring plan will be developed based on the trial risk assessment. It may include on-site monitoring and will be agreed upon by the trial steering committee, and principal investigators. The clinical research organization (Metanoic Health Ltd) will arrange an independent monitor, separate from investigators and the sponsor, to ensure compliance with trial protocols and policies, participant protection, and accurate data collection.

Adverse events (AEs) and serious adverse events (SAEs) will be recorded throughout the study. Participants will be interviewed at each visit to investigate signs or symptoms. Participants will also be encouraged to report AEs/SAEs at any time. The investigator will gather sufficient information to determine the outcome and causality of AEs/SAEs and promptly notify the competent authority if necessary. Follow-up of AEs/SAEs will be required after the study's discontinuation if they persist or have sequelae.

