## Study population

Participants will be recruited on a voluntary basis from a group of cigarette smokers who have been clinically diagnosed with T2D. Only patients who smoked daily for at least 5 years will be considered for inclusion in the study. To confirm the smoking status of potential participants, an exhaled carbon monoxide (eCO) measurement will be taken at the screening visit. The cutoff for confirmation as a smoker will be an exhaled CO level greater than or equal to 7 parts per million (ppm). To avoid including patients with poorly controlled diabetes requiring immediate modification of therapy, it was decided to set a glycated hemoglobin percentage of between 6 and 12% as an inclusion criterion. Another criterion is a BMI between 17.6 kg/m^2^ and 34.5 kg/m^2^ to achieve greater homogeneity of the group and to avoid subjects with morbid obesity and coexisting other metabolic disorders, which could affect the outcome of the study. Each participant identified as a smoker with T2D will be offered access to free smoking cessation programs aimed at helping participants quit smoking. Only those who refuse to participate in the smoking cessation programs and express willingness to switch to C-F NA will be eligible for randomization. Before randomization, participants will provide informed consent.

Participants will be required to satisfy all of the following criteria.

Inclusion criteria:Men or women diagnosed with T2D (as defined by the American Diabetes Association).Cigarette smokers of ≥ 10 cigarettes/day (max 30 cigarettes/day).History of regular smoking for at least 5 consecutive years.Verified smoking status (eCO ≥ 7 ppm).Willingness to switch to a C-F NA.Refusal to participate in smoking cessation programs.Glycated hemoglobin between 6 and 12%.Body mass index between 17.6 kg/m^2^ and 34.5 kg/m^2^, both inclusive.Body weight exceeding at least 50 kg (men) or 40 kg (women).

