**Fig. 1 Fig1:**
[figure not shown]
Study design flow of DiaSmokeFree; *V* visit, *C-F NA* combustion-free nicotine alternatives

Participants will attend a screening visit within 28 days prior to study visit 1 (Tables 1 and 2). During the screening visit, socio-demographic data, detailed medical history (including medication use), and detailed history of smoking, vaping, and heated tobacco products (HTPs) use will be collected. Additionally, participants’ intention to quit smoking will be assessed. All patients will be offered a smoking cessation program according to the local guidelines. A second opportunity to enroll in a free smoking cessation program will be offered before study enrollment. Any participant who expresses the intention of booking for the cessation program or to quit smoking in the next 6 months will be urged to do so and not be recruited in the study. Patients taking part in the study will be informed that they are free to quit smoking and withdraw from the study at any time. Moreover, participants will be encouraged to quit smoking at every contact time point throughout the whole study.

**Table 1 Tab1:** Study assessments (Control group—Arm A)

Procedure	Screen (V0)	Baseline (V1) day 1	Week 12 (V2) day 90 ± 5	Week 24 (V3) day 180 ± 7	Week 52 (V4) day 360 ± 7	Week1 04 (V5) day 720 ± 7
Eligibility criteria check	X	X				
Medical Hx	X					
Medication use		X	X	X	X	X
Smoking/vaping Hx	X					
Cigarette consumption	X	X	X	X	X	X
Exhaled CO		X	X	X	X	X
FTND		X				
Intention to quit	X	X				
Informed consent		X				
Randomization		X				
Tracker APP installation		X				
Vital signs		X	X	X	X	X
Weight, BMI, waist circumference		X	X	X	X	X
Body composition equation*		X	X	X	X	X
QoL questionnaire		X	X	X	X	X
Smoking cessation advice	X	X	X	X	X	X
Spirometry		X				X
Metabolic syndrome assessment**		X	X	X	X	X
Blood sample***		X	X	X	X	X
Testosterone (men only)		X	X	X	X	X
Urine albumin to creatinine ratio (ACR)						
Safety reporting		X	X	X	X	X

*BL* baseline, *V* visit, *Hx* history, *CO* carbon monoxide, *BMI* body mass index, *FTND* Fagerstrom Test for Nicotine Dependence, *QoL* quality of life, *CBC* complete blood count, *WBC* white blood cells, *Hb* hemoglobin, *LDL* low-density lipoprotein, *HDL* high-density lipoprotein, *HbA1*_*C*_ glycated hemoglobin, *AE/SAE* (serious) adverse incidents

*Body composition (fat and skeletal muscle mass) by validated equation by Lean ME et al. (1996) and Al-Gindan YY et al. (2014)

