After randomization, participants’ smartphones will be equipped with a dedicated tracker application. This application is designed to monitor individual behaviors such as physical activity, adherence to capillary blood glucose monitoring, cigarette smoking frequency and daily C-F NA usage. The tracker application will also identify any protocol violations, collect adverse events and send reminders (e.g., next scheduled appointment, study restrictions, instructions) throughout the study duration. The use of a dedicated tracker application adds an innovative element to continuously collect data and enhances adherence to the study protocol.

After the baseline assessments (Visit 1), participants will be invited to attend four more clinical visits (Visits 2–5), which will be conducted in an ambulatory (outpatient) setting. During these visits, a number of measurements will be taken, with a particular focus on metabolic syndrome parameters, i.e., waist circumference, systolic blood pressure value, venous blood concentration of triglycerides, HDL, and fasting blood glucose (Tables 1 and 2). Also, two questionnaires will be used.

(Diabetes Quality of Life questionnaire and the Fagerström Test for Nicotine Dependence) to assess specific aspects of participants' health and smoking behavior.

Following each clinical visit, participants will be provided with an appropriate number of consumables (cartridges/pods or e-liquids refill bottles for e-cigarettes, tobacco sticks for HTPs) if they are in the intervention arm (Arm B). Participants in the intervention arm will have additional non-clinical visits between the clinical visits. These non-clinical visits are designed to replace any used consumables and provide an opportunity for study investigators to stimulate retention and check compliance. At these non-clinical visits, participants in Arm B will be required to return all empty, part-used, and unused consumables from the previous study period. This evaluation of the habitual pattern of C-F NA use and verification of product adherence are essential for monitoring the participants' compliance with the intervention.

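### Adverse-event questioning can be read as 17 vs 4 or as 4 vs 4 interviews, and C-F NA use has no scheduled visit assessment in the control arm

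*Protocol article*

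**What the plan says.** **Visits.** Both arms have clinical visits V2 to V5 after baseline, at weeks 12, 24, 52 and 104 (Tables 1 and 2). The Study design section adds: "Participants in the intervention arm will have additional non-clinical visits between the clinical visits". It gives their purpose: "These non-clinical visits are designed to replace any used consumables and provide an opportunity for study investigators to stimulate retention and check compliance". Safety is not named among the purposes.

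**Adverse events.** The section on data monitoring and study safety says "Participants will be interviewed at each visit to investigate signs or symptoms" and "Participants will also be encouraged to report AEs/SAEs at any time". In both tables the row "Safety reporting" is marked at V1 to V5 only; in Table 2 it is blank at every non-clinical visit. The Study design section also says "The tracker application will also identify any protocol violations, collect adverse events and send reminders", and both tables schedule the app's installation at baseline.

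**C-F NA use.** Under Study population, only people who decline the cessation programmes and "express willingness to switch to C-F NA will be eligible for randomization". Table 2 has a row for C-F NA use at every post-baseline contact; Table 1 has no such row. Controls give a smoking and vaping history at screening only. After that, their visits record cigarette consumption and exhaled CO. The app is described as tracking daily C-F NA use, with no restriction to one arm. Objectives and end points states that the assessments at each time point are done in all participants of both arms.

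**The concern.** Two points about unequal observation need settling.

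The first is safety. The text asks about symptoms at each visit, and the article itself calls Arm B's interim contacts visits. Table 2 schedules no safety reporting at those contacts. A site could follow either and be in line with part of the protocol. Participants and staff know the allocation, and the trial is meant to inform on the risks as well as the benefits of C-F NA. If one arm is asked more often, a difference in recorded events may partly reflect how often people were asked.

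The second is control-arm uptake. Every control was willing to switch before being allocated to usual care, and these are marketed products. Under Statistical analyses, all randomised controls stay in the full analysis set. The confounders listed there include smoking but not C-F NA use. Without a visit-level record, a reader of the results could not tell with confidence how many controls took up the products under study.

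**Working it through.** **1. Contacts, counted from the table columns.**

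- Arm A: weeks 12, 24, 52, 104 = 4. This agrees with the Study design text, which announces four further clinical visits.
- Arm B: those 4, plus weeks 2, 4, 8, 20, 32, 40, 48, 60, 68, 76, 84, 92, 100 = 13 non-clinical visits. 4 + 13 = 17.
- Longest gap between contacts: 8 weeks in Arm B, and 104 − 52 = 52 weeks in Arm A.

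**2. What each text implies after baseline.**

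| Item | Arm A | Arm B |
|---|---|---|
| Safety-reporting rows of Tables 1 and 2 | 4 | 4 |
| Interview at each visit, non-clinical visits included | 4 | 17 |
| C-F NA use rows | 0 (no row) | 17 |

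The interview ratio is 4/4 = 1.0 on the first reading and 17/4 = 4.25 on the second.

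**3. What the second reading could mean for recorded events (illustration only).** Assume that an interview captures events from a recall window of w weeks before it. The documents give no such window. The share of the 104 weeks covered is the sum of min(w, gap) over the gaps, divided by 104. The gaps are 12, 12, 28, 52 in Arm A. In Arm B they are 2, 2, 4, 4, 8, 4, 8, 8, 8, 4, 8, 8, 8, 8, 8, 8, 4.

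| w (weeks) | Arm A | Arm B | Ratio B:A | Ratio if app or spontaneous reports catch 50% of the rest |
|---|---|---|---|---|
| 4 | 16/104 = 15% | 64/104 = 62% | 4.0 | 1.4 |
| 8 | 32/104 = 31% | 100% | 3.25 | 1.5 |
| 12 | 48/104 = 46% | 100% | 2.2 | 1.4 |
| 26 | 76/104 = 73% | 100% | 1.4 | 1.2 |

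The last column is (b + (1 − b) × 0.5) / (a + (1 − a) × 0.5), where a and b are the shares for Arms A and B. The 50% is also an assumption. At 25% caught the ratios run from 1.25 to 2.08 over these windows; at 75% they run from 1.07 to 1.21. If interviews follow the table rows, the ratio is 1.0 for every window.

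**4. Can the other control measures identify switching?** A control who switches completely and one who quits completely both report no cigarettes, and exhaled CO marks smoke exposure, so neither measure separates them. The Study design section lists a decision to stop smoking completely among the grounds for premature withdrawal, and it does not list switching. The two kinds of control can therefore leave or stay for different reasons while looking alike on the visit data. Only the app is described as recording C-F NA use in controls, and no scheduled visit question checks it.

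**The case against.** The strongest reply on safety is that the tables already settle the matter. Scheduled safety reporting is 4 against 4. The extra contacts are labelled non-clinical and serve resupply, retention and compliance, so the interview rule can be read as meaning clinical visits. Both arms may report events at any time and have the app. The article also specifies no between-arm test of adverse events, and that detail may properly sit in the analysis plan. Most of this stands. A reader might infer from 17 against 4 that the safety comparison is biased about fourfold. The documents do not support that, because the figure needs one of two available readings. What remains is that the two texts are not reconciled. Even if Table 2 governs, 13 further staff contacts give Arm B more occasions to mention an event.

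On uptake, a reader might infer that switching among controls is hidden. That too goes further than the documents: the app covers both arms, and cigarette counts and exhaled CO at four visits would flag a control who gave up cigarettes. The full protocol may hold further CRF questions. Against this, the article prints both schedules row by row, and only one has the C-F NA use row. The statement that assessments are done in both arms stands in the paragraph on secondary end points and could be read as limited to those. On its plain wording, it conflicts with Table 1.

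It is also tempting to convert control switching into lost power. The documents give no uptake rate, and recording uptake would not restore power. Nor is it an error that Arm B receives more contact: the article discloses the resupply visits as part of delivering the intervention.

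**Conclusion.** The point holds in a limited form.

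- **Safety.** The safety text and Table 2 allow either 17 vs 4 or 4 vs 4 post-baseline interviews. In an open-label trial this is a risk of differential ascertainment, with more recorded events in Arm B as the likely direction. Its size cannot be fixed from the documents. It is nil for scheduled questioning if the table rows govern. If every contact includes an interview, it depends on recall and on how much the app and spontaneous reports capture, both of which are assumptions here.
- **Control uptake.** C-F NA use is scheduled 17 times in Arm B and never in Arm A, in a population selected for willingness to switch. Uptake among controls is under-ascertained: the app may record it, but no visit assessment backs the app, and the visit measures cannot separate switching from quitting.

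The sample size of 576 is not affected.

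**What to change.** 1. Add C-F NA use at V2–V5 to Table 1, with the same questions as in Arm B, and report control-arm uptake by visit.
2. State whether adverse-event interviews take place at the non-clinical visits, and bring the safety section and Tables 1 and 2 into agreement.
3. Base the between-arm adverse-event comparison on one question asked in the same words at V2–V5 in both arms, covering the whole interval since the previous clinical visit. The whole-interval wording is essential. Without it, an Arm B event already noted at an interim visit might not be raised again at the next clinical visit, and Arm B would be undercounted.
4. Show events from other sources (interim visits, app, spontaneous reports) separately by source, and keep all events in safety review.

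The cost is one extra CRF question at four existing control visits, some wording and a little more tabulation. Two limits remain. Recall over the 52 weeks from V4 to V5 will be imperfect in both arms. For control visits already held, the question cannot be asked in retrospect with the same reliability; there, the available app records should be reported as the source.

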### Ethical considerations and results dissemination

The study will adhere to the principles of Good Clinical Practice and the Declaration of Helsinki. It has been reviewed and approved by seven ethics committees. Relevant documentation, such as the informed consent form and patient information sheet, has been translated where necessary. The informed consent material will be obtained by site investigators through relevant forms. The chief investigator will be responsible for deciding whether amendments to the protocol are substantial or non-substantial. Substantial amendments will be submitted to the research ethics committee for approval before implementation.

In the UK, all investigators and trial site staff will comply with the Data Protection Act 2018 regarding the collection, storage, processing, and disclosure of personal information. In other countries, equivalent local data protection regulations will be followed.

The trial steering committee (TSC) will have access to the full trial data set. Site investigator(s) will need formal approval from the TSC and sponsor for data access requests. Committee members are independent and have no conflicts of interest.

The intention is to disseminate the study results through articles in peer-reviewed journals and conference presentations. A summary of results will be available on the Ashford and St Peter’s Hospitals’ website for public access. The anonymized data will be available to researchers upon request, following approval from the established scientific committee.

## Results

Patient recruitment has started in September 2021 and enrolment is expected to be completed by December 2023. Results will be reported in 2026.

## Discussion

Smoking cessation is a priority for patients with T2D and the use of C-F NA has grown exponentially in the past decade. However, there is limited knowledge regarding the overall health impact of C-F NA like e-cigarettes and HTPs on individuals with T2D who smoke. The DiaSmokeFree study will be the first trial to address this knowledge gap. The study has been specifically designed to tests the hypothesis that avoiding exposure to cigarette smoke toxicants by substituting tobacco cigarettes for C-F NA may lead to measurable amelioration in cardiovascular risk factors and metabolic parameters, compared to individuals who continue smoking tobacco cigarettes.

Although it is generally desirable, and in particular for individuals with T2D who smoke to stop any form of tobacco consumption, devices that deliver nicotine without combustion (i.e., C-F NA) are de facto replacing tobacco cigarettes among smokers worldwide [39–44]. Compared with tobacco cigarettes, they offer substantial reduction in exposure to toxic chemical emissions [45–49]. For this reason, they are proposed for harm reduction from cigarette smoke and for smoking cessation [18, 21, 50, 51]. However, C-F NA are not risk free, and they might have adverse health effects not yet identified.

DiaSmokeFree's study design was based on the idea that C-F NA are marketed as substitutes for tobacco cigarettes and that the reference product would be participants’ own brand tobacco cigarettes. The study duration of 24 months allows for observation of changes in the primary end point, and the randomized design ensures high-quality data by equalizing variation in smoking history and other variables between the study arms. Additionally, the welfare of participants is emphasized throughout the study with regular reminders to quit smoking and access to free smoking cessation programs.

Several of the parameters measured in this study are associated with the development of cardiovascular diseases (e.g., hypertension, elevated blood cholesterol, and BMI > 25), and some of these parameters have been shown to improve relatively quickly after smoking cessation [34, 35]. Therefore, the profile of these changes after switching to C-F NA may provide valuable insight into the overall potential of these products to reduce the overall cardiovascular risk.

The introduction of several compliance checkpoints throughout the study to record the consumption of tobacco cigarettes and use of C-F NA is a significant feature of the study. Ensuring compliance with the study protocol is crucial for obtaining reliable results as failure to replace conventional cigarettes fully or largely with C-F NA would reduce or nullify the expected changes in study end points. Participants will be encouraged to adhere to their assigned intervention and reduce conventional cigarette consumption by at least 80% from baseline. They also will be informed that a compliance check will be performed at each visit through biochemical verification. Compliance will be also checked by counting all empty, partially used and unused consumables returned at each visit (i.e., consumables record checks) and by reviewing any non-compliance recorded in the research diary or via the tracker app.

Although compliance in this study is not expected to differ significantly compared to other similar studies, our power calculation is overestimated, to take account of a non-compliance rate of 50%. Therefore, the C-F NA population will be oversampled using a 1:2 randomization ratio scheme (i.e., for every patient randomized in the control population, two patients will be randomized in the C-F NA population). Finally, by requiring participants to return to the clinic to regularly stock up on cartridges/pods or e-liquids refill bottles for e-cigarettes, and tobacco sticks for HTPs will also increase study participation and retention in the C-F NA population.

The study’s innovative features include offering participants a range of C-F NA options to choose from, ensuring a user-friendly experience, and increasing the likelihood of adoption. This element of choice is missing from any switching trials to date, in which a single product is generally offered. Since DiaSmokeFree's population sample consists mainly of elderly patients, we will provide devices that ensure the most user-friendly experience possible (e.g., easy-to-refill consumables, pre-filled consumables, etc.). This approach enhances generalizability and makes the findings applicable to a broader population.

Another significant feature that makes this study unique is the incorporation of an innovative tracker application designed to monitor various behaviors and enhance adherence to the study protocol. The application serves multiple functions, including monitoring physical activity, adherence to capillary blood glucose monitoring, cigarette smoking frequency and daily C-F NA usage. By continuously collecting data through the tracker application, researchers can closely monitor participants' behaviors and identify any protocol violations. This real-time monitoring allows for prompt intervention or corrective measures to maintain adherence and ensure the integrity of the study. Additionally, the tracker application enables the collection of adverse events, which provides valuable information on the safety and tolerability of C-F NAs. Researchers can promptly address any adverse events and take necessary actions to safeguard participant well-being. Furthermore, the application serves as a communication tool, sending reminders to participants about their next scheduled appointment, study restrictions, and instructions. These reminders help to keep participants engaged and informed throughout the entire duration of the study.

As with any study, our protocol has limitations. First, subject retention in the study can be challenging due to the relatively long follow-up (24 months). Nonetheless, inviting participants to return to the clinic with study equipment provided free of charge and a dedicated fast-track approach to their outpatient appointments may increase study participation and retention. Second, the results of DiaSmokeFree cannot be extrapolated to all smokers with diabetes. We will not recruit smokers with untreated disease or with acute complications of T2D. Also, individuals with Type 1 Diabetes (T1D) will be excluded from the study. The impact of COVID-19 restrictions on recruitment is also acknowledged, and strategies will be implemented to mitigate any potential drawbacks.

